#### Dropout criteria

2.4.4

Participants will drop out of the trial under the following conditions:

(1)do not cooperate with the specified treatments or reluctance to continue the trial;(2)objective factors cause data loss or incompleteness that could influence the record of observation indicators;(3)serious diseases (such as cardiocerebrovascular, liver and kidney diseases) were found during the treatment;(4)participants who take drugs which have an impact on body weight or appetite during the treatment;(5)significant deviation in implementation or large error in protocol; or if participants accept any other way to lose weight during treatment.

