### Blinding and informed consent

2.6

In this study, the participants will be informed that they will have a 1/3 chance of being allocated to receive 1 of the 3 treatments: heat application, medicated plaster, and herb-partitioned moxibustion. The data statisticians and research staff involved in data collection and data analysis will be blinded to the assignment of participants’ group throughout the entire study. However, the participants and therapists cannot be masked due to the nature of these interventions, but they will be trained not to share any information with other participants, researchers, and the data statistician regarding treatment procedures and responses.

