### Statistical analysis

2.12

The data of all participants will be conducted in the final statistical analysis which will be in accordance with the per-protocol principle and the intent-to-treat principle. The data statisticians will be blinded to the group allocation. The SPSS software v19.0 (Statistics 19.0, SPSS, IBM Corp., Chicago, IL) will be used for statistical processing. Measurement data will be presented in the form of mean ± standard deviation, while count data will be expressed as percentage and number. The continuous variables, such as participants’ obesity-related indicators including weight, BMI (weight/height), body fat percentage, basic metabolism value, WC, HC, waist-to-hip ratio (WC/HC), visceral fat area, body fat, and obesity degree will be presented as mean ± SD. Between-group comparisons will be performed by ANOVA or its non-parametric equivalents on changes from baseline to after treatment. Intra-group comparison will be performed by using the Kruskal–Wallis test. All statistical tests will be performed on both sides, and the difference will be considered statistically significant when *P* < .05.

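### The dropout rules end trial participation, not only treatment, so the promised intent-to-treat analysis may lack week-4 outcomes that could have been collected

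*Protocol article*

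**What the plan says.** Dropout criteria (2.4.4) begins: "Participants will drop out of the trial under the following conditions". Apart from serious disease found during treatment, which is a clinical ground and is left aside here, the grounds are:

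- (1) "do not cooperate with the specified treatments or reluctance to continue the trial"
- (2) "objective factors cause data loss or incompleteness that could influence the record of observation indicators"
- (4) "participants who take drugs which have an impact on body weight or appetite during the treatment"
- (5) "significant deviation in implementation or large error in protocol; or if participants accept any other way to lose weight during treatment"

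Statistical analysis (2.12) states "The data of all participants will be conducted in the final statistical analysis" and that this will be "in accordance with the per-protocol principle and the intent-to-treat principle".

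Three other places matter. Primary outcomes (2.8.1) sets the effectiveness rating at week 4. Blinding and informed consent (2.6) says that "the participants and therapists cannot be masked due to the nature of these interventions". Sample size calculation (2.11) assumes effective rates of 0.80 (moxibustion), 0.65 (heat) and 0.60 (plaster), and raises 33 per group to 36 for 10% withdrawal.

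**The concern.** Intent-to-treat needs an outcome, or a defensible substitute for one, from everyone randomised. The listed grounds are mostly what a trial would use to define its per-protocol set. Written as exits from the trial, they invite staff to stop collecting data on exactly those people whose outcomes the intent-to-treat analysis needs.

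The losses would not be random. Someone who stops cooperating or turns to another weight-loss method has plausibly responded poorly. Because participants know their arm, interest may fade faster in one arm than in another. Non-cooperation and significant deviation are also judgements without a stated threshold, in a trial where therapists know the allocation.

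Criterion 2 is the least defensible. It makes missing data a reason for removal, when intent-to-treat calls for the person to be kept and the gap handled. What is at stake is the primary comparison: a later analysis plan can model uncollected week-4 outcomes but cannot recover them.

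**Working it through.** **The texts side by side.** Section 2.4.4 ends participation in the trial. It draws no line between stopping treatment and leaving follow-up, and no section says that those who drop out are still measured at week 4. Section 2.12 brings in all participants. The two fit together only if follow-up continues after a dropout criterion is met, and the article does not say that it does. The 10% allowance in 2.11 suggests that withdrawals are expected to be lost.

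**The plan's own figures.** The planned differences are 0.80 − 0.65 = 0.15 and 0.80 − 0.60 = 0.20. On the allowance, 33/0.9 = 36.7 against the planned 36, a trivial rounding gap. The plan gives no figure for bias, so there is none to reproduce. Whether 33 per group is itself right is a separate matter that does not bear on this point.

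**Illustration 1: non-responders lost and left out.** Assumptions: the planning rates are the true rates in everyone randomised; a fraction d = 0.10 of an arm is lost; all those lost are non-responders; the analysis omits them. The observed rate in that arm is then p/(1 − d):

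- moxibustion: 0.80/0.90 = 0.889
- heat: 0.65/0.90 = 0.722
- plaster: 0.60/0.90 = 0.667

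| Where the 10% is lost | Moxibustion − heat (planned 0.15) | Moxibustion − plaster (planned 0.20) |
|---|---|---|
| Both arms | 0.889 − 0.722 = 0.167 | 0.889 − 0.667 = 0.222 |
| Comparator only | 0.80 − 0.722 = 0.078 | 0.80 − 0.667 = 0.133 |
| Moxibustion only | 0.889 − 0.65 = 0.239 | 0.889 − 0.60 = 0.289 |

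**Illustration 2: no true difference.** Two arms of 36, both truly 0.65, so 0.65 × 36 = 23.4 responders each. In total 7.2 non-responders (10% of 72) are lost and omitted:

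- 3.6 and 3.6 lost: 23.4/32.4 = 0.722 in each arm, difference 0
- 1.8 and 5.4 lost: 23.4/34.2 = 0.684 and 23.4/30.6 = 0.765, difference 0.08
- 0 and 7.2 lost: 0.65 and 23.4/28.8 = 0.8125, difference 0.16

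**Illustration 3: bounds for an analysis of everyone randomised.** Here the planning rates are taken to hold in the 32.4 per arm who are observed, and 3.6 per arm are missing. Responders observed are 0.80 × 32.4 = 25.92 and 0.65 × 32.4 = 21.06.

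- Least favourable to moxibustion: 25.92/36 − (21.06 + 3.6)/36 = 0.72 − 0.685 = 0.035
- Most favourable: (25.92 + 3.6)/36 − 21.06/36 = 0.82 − 0.585 = 0.235

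An intent-to-treat estimate could lie anywhere in that range, depending on what is assumed about the missing outcomes.

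**The case against.** A reader might infer that those who drop out have no week-4 assessment, that the intent-to-treat set is therefore the completers, and that an unbiased intent-to-treat analysis is impossible. The documents do not support this. Section 2.4.4 says neither that assessments stop nor that anyone is excluded from analysis, and 2.12 keeps the data of all participants. The syndrome score behind the primary outcome is planned at weeks 0 to 4 (Table 1 and 2.8.4), so a person who leaves midway would normally have earlier scores. That part of the objection stands.

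It is also fair that a condensed article may leave the choice of primary analysis set and the missing-data rule to the full protocol or SAP. Their absence here is not a fault in itself. Reluctance to continue is partly ordinary withdrawal, and criterion 2 could be read as a loose description of loss to follow-up.

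Outcome evaluators, data staff and statisticians are blinded (2.5, 2.6, 2.12), and no section says that therapists decide who drops out. Blinded assessment protects how outcomes are measured, however, not who remains to be measured.

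Lastly, the figures above are extremes by construction. Equal loss in both arms moves the planned 0.15 by only 1.7 points, and loss in the heat arm alone works against moxibustion. It would be wrong to cite them as evidence that the rule favours the experimental arm.

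What remains is a stated rule that, as worded, ends participation for post-randomisation events and sits badly with the promise in 2.12.

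**Conclusion.** The point holds as a conflict between 2.4.4 and 2.12 that should be fixed. Followed as written, the dropout rule creates avoidable missing week-4 primary outcomes, likely related to prognosis and possibly to arm. The intent-to-treat analysis would then depend on assumptions that the data cannot test. It does not follow that the analysis is impossible or certainly biased.

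Neither the size nor the direction of the bias can be fixed in advance. At 10% loss, with every lost participant a non-responder omitted from the analysis, the planned 0.15 against heat becomes 0.078, 0.167 or 0.239, depending on where the loss falls. If the arms are truly equal and the losses balanced, no spurious difference arises. These results rest on the planning rates, on applying the general 10% allowance arm by arm, on effective meaning any grade better than the lowest, and on the assumed identity of those lost.

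**What to change.** Reconcile 2.4.4 with 2.12:

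- Leave the reasons for ending treatment unchanged. State that a participant who meets one stays in follow-up, has the existing week-4 assessment unless consent is withdrawn, and is analysed in the arm allocated.
- Use the criteria only to define the per-protocol set.
- Delete data incompleteness as a ground for removal.
- Name intent-to-treat as the primary analysis and per-protocol as supportive, if the full protocol or SAP does not already do so. The rule for outcomes still missing belongs there too. Counting them as not effective is one convention, but it is not neutral when loss differs between arms.

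The cost is a short amendment to two sections and slightly more follow-up effort for a visit that is already scheduled. The planned 36 per group does not change. The effect estimate may be smaller than one based on completers.

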### Randomization and allocation concealment

2.5

The web-based online randomization system to be adopted in this study will be performed by an independent Evidence-based Research Centre at Central South Hospital Affiliated to Wuhan University. Eligible patients will be identified by the attending physicians according to the inclusion and exclusion criteria. Eligible subjects who have written an informed consent will be randomly assigned to 1 of these 3 groups. The randomization list is kept by the research coordinator and biostatistician until the end of the trial, the aim of which is to ensure allocation concealment; all the researchers who evaluate the results above will not be aware of which group the participants have been assigned to. All processes will be recorded and saved as appropriate.

### Blinding and informed consent

2.6

In this study, the participants will be informed that they will have a 1/3 chance of being allocated to receive 1 of the 3 treatments: heat application, medicated plaster, and herb-partitioned moxibustion. The data statisticians and research staff involved in data collection and data analysis will be blinded to the assignment of participants’ group throughout the entire study. However, the participants and therapists cannot be masked due to the nature of these interventions, but they will be trained not to share any information with other participants, researchers, and the data statistician regarding treatment procedures and responses.

### Intervention

2.7

#### Lifestyle modification treatment

2.7.1

The following lifestyle modification are recommended to help to establish healthy habits:

(1)firstly, the basal metabolic value of patients will be calculated based on the formula of BMR according to body weight recommended by FAQ/WHO;(2)according to the basic metabolic value, we can get the difference between the daily intake of diet calories and exercise consumption calories, that is: the intake of dietary calories-exercise consumption of calories ≤ the basic metabolic value;(3)according to the difference between the calculated dietary calories and exercise calories, all participants will be prescribed an appropriate diet and exercise programs, which is formulated according to requirements of dietary guidelines for Chinese residents approved and issued by the Standing Council of Chinese Nutrition Society. The proportion of 3 nutrients in total calories comprises of 55% to 65% from carbohydrates, 20% to 30% from oils and 15% from protein, and the energy of the whole day distributed to 3 meals will follow the proportion of 30% for breakfast, 40% for lunch, and 30% for dinner. Meanwhile, all participants will be instructed to record their food and calorie intake daily, and low-to-moderate intensity physical activities such as jogging, walking, and swimming will be instructed to them for at least 5 days per week continually, 30% to 50% of the maximum heart rate reserve value will be required. The maximum heart rate reserve value = the patient's maximum heart rate (220-age)-the patient's static heart rate (the heart rate when the patient wakes up in the morning but has not yet got up).

All patients will be instructed to keep a diet and exercise diary.

The intervention time of lifestyle modification treatment will last for 8 weeks.

#### Heat application group

2.7.2

The acupoints will be selected as Tianshu, Pishu, shenshu, zhongwan, and zusanli. The location of the acupoints were based on the national GB/T 12346-2006 acupoints standard.^[17]^ The hot sticker will be placed on the patient's acupoints for about 2 hours. This treatment will be applied once every other day, 3 times per week, for 4 consecutive weeks. The treatment will be delayed during the menstrual period.

#### Medicated plaster group

2.7.3

The acupoints will be selected as Tianshu, Pishu, shenshu, zhongwan, and zusanli. The location of the acupoints were based on the national GB/T 12346-2006 acupoints standard.^[17]^The Chinese traditional medicine (aconite root, dried ginger, evodia rutaecarpa, clove, cinnamon, etc) in moderation will be grinded into powder, and the powder will be added with a certain amount of flour, and finally they will be blended with ginger juice to the appearance of mud. Next, 10 g of the kneaded medicine mud will be taken and applied to the bottom of the ordinary sticker. They will be placed on the patient's acupoints for about 2 hours. The sticker has the same shape as the hot sticker, but it does not have the effect of thermal stimulation and infrared radiation. This treatment will be applied once every other day, 3 times per week, for 4 consecutive weeks. The treatment will be delayed during the menstrual period.

#### Herb-Partitioned moxibustion group

2.7.4

The acupoints will be selected as Tianshu, Pishu, shenshu, zhongwan, and zusanli. The location of the acupoints were based on the national GB/T 12346-2006 acupoints standard.^[17]^ The Chinese traditional medicine (aconite root, dried ginger, evodia rutaecarpa, clove, cinnamon, etc) in moderation will be grinded into powder, and the powder will be added with a certain amount of flour, and finally they will be blended with ginger juice to the appearance of mud. Next, 10 g of the kneaded medicine mud will be taken and applied to the bottom of the hot sticker. They will be placed on the patient's acupoints for about 2 hours. This treatment will be applied once every other day, 3 times per week, for 4 consecutive weeks. The treatment will be delayed during the menstrual period.

### Outcome measures

2.8

#### Primary outcomes.

2.8.1

The clinical effectiveness of 4 weeks of

Heat application group,Medicated plaster group, andHerb-partitioned moxibustion group for the improvement of simple obesity will be assessed and determined by the clinical evaluation of nimodipine:

(1)Healing: the clinical symptoms disappear or almost disappear, and the syndrome score is reduced by ≥85%;(2)Significant effect: the clinical symptoms are obviously improved, and the syndrome score is reduced by <85%, but ≥50%;(3)Effective: the clinical symptoms have improved, syndrome scores decreased by <50%, but ≥30%;(4)Invalid: the clinical symptoms were not improved, even worse, and the syndrome score was reduced by <30%.

Integral variation formula (Nimodipine method: [(pre-treatment score-post-treatment score)/pre-treatment score] X100%. This index will be assessed on week 4.

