#### The syndrome score of TCM

2.8.4

The syndrome score of TCM will be adopted as the criterion of syndrome determination according to the diagnostic and therapeutic evaluation standard of simple obesity revised by the 5th National Obesity Research Conference in 1997. The total score will be then calculated and the unit will be expressed in points. The main clinical symptoms of simple obesity of spleen deficiency and dampness resistance type were divided into 4 levels, which include no (0 point), mild (1 point), medium (2 points) and heavy (3 points). Measurements will be made on week 0, 1, 2, 3, 4.

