### Sample size calculation

2.11

In a previous study, the effective rate of simple obesity in the herb-partitioned moxibustion group was *P*1 = .80. The effective rate of the heat application group was *P*2 = .65, and the effective rate of the medicated plaster group was *P*3 = .6. PASS V.11 software (NCSS, Kaysville, UT) was used to calculate that, based on 80% power to detect a significant difference(α = 0.025, 1 sided), 33 participants will be required for each group. Allowing for a 10% withdrawal rate, we plan to include a total of 108 participants with 36 participants in each group.

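### The trial is sized on a yes/no effective rate although the primary outcome has four ordered grades and the score behind them is recorded in full; testing the collapsed rate would cost about 9 to 22 points of power per comparison

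*Protocol article*

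**What the plan says.** Section 2.8.1 takes the pre-to-post fall in the syndrome score as a percentage of the pre-treatment score. At week 4 it assigns one of four grades, with cuts at 85%, 50% and 30%. The third grade reads "Effective: the clinical symptoms have improved, syndrome scores decreased by <50%, but ≥30" per cent, and anything below 30% is labelled invalid. Each grade also carries a short description of how the clinical symptoms changed.

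Section 2.8.4 lists the TCM syndrome score as a further outcome, measured at weeks 0, 1, 2, 3 and 4: "The total score will be then calculated and the unit will be expressed in points".

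Section 2.11 sizes the trial on proportions: "the effective rate of simple obesity in the herb-partitioned moxibustion group was *P*1 = .80"; "The effective rate of the heat application group was *P*2 = .65"; "the effective rate of the medicated plaster group was *P*3 = .6". The calculation is "based on 80% power to detect a significant difference(α = 0.025, 1 sided", giving 33 per group, raised to 36 for withdrawals.

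Section 2.12 names ANOVA or a non-parametric equivalent on change from baseline for between-group comparisons, and adds: "All statistical tests will be performed on both sides". It does not say how the four grades are to be compared.

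**The concern.** The same measurement appears at three levels of detail: a points total, four ordered grades, and a yes/no rate. The primary outcome uses the second and the sample size uses the third. The article gives no reason for leaving the first. The conference standard cited in 2.8.4 is invoked for determining and scoring the syndrome, while 2.8.1 attributes the response formula only to the nimodipine method.

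Each step down discards information. With four grades, a fall of 31% and one of 49% count alike, and a fall of 29% counts the same as a worsening. If the grades are then merged into effective versus invalid, the top three also become one. In a trial of 36 per arm that its own Discussion calls small, a real advantage of the assumed size would be missed more often than it need be, with data already collected.

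**Working it through.** **Inputs.** Effective rates 0.80 (herb-partitioned moxibustion), 0.65 (heat) and 0.60 (plaster), 80% power, one-sided 0.025, 33 evaluable and 36 planned per arm, all from 2.11. Cuts at 30%, 50% and 85% from 2.8.1. One-sided 0.025 in 2.11 and two-sided 0.05 in 2.12 share the critical value 1.96, so that difference does not affect the figures.

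**Two readings.** The effective rate is not defined. I take it as the proportion with a fall of at least 30%, because 2.8.1 calls everything below that invalid. I take the syndrome score of 2.8.1 to be the TCM score of 2.8.4.

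**Step 1: the plan's own figure.** n per group = [1.960·√(2p̄(1−p̄)) + 0.842·√(p1(1−p1)+p2(1−p2))]² / (p1−p2)².
- Heat: p̄ = 0.725; (1.960 × 0.6315 + 0.842 × 0.6225)² / 0.15² = 3.103 / 0.0225, so 138.
- Plaster: p̄ = 0.70; (1.960 × 0.6481 + 0.842 × 0.6325)² / 0.20² = 3.249 / 0.04, so 82.

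The stated 33 does not reproduce. Continuity-corrected, unpooled, arcsine, other alpha levels and a three-group chi-square were also tried; the lowest result was 62. This is a separate and larger defect, but it sets the starting point: power on the yes/no scale is far below 80%.

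**Step 2: yes/no rate.** Exact enumeration of the pooled two-proportion z test, rejecting above 1.96.

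**Step 3: full scale.** The documents give no SD or distribution, so a model must be assumed. If the percentage fall is normal with equal SD and is cut at the same point in each arm, the rates imply a standardized difference d = z(0.80) − z(p2), whatever the SD:
- Heat: 0.842 − 0.385 = 0.456 (from unrounded values).
- Plaster: 0.842 − 0.253 = 0.588 (likewise).

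Power then comes from the noncentral t distribution. With a logistic distribution instead, d = 0.423 and 0.541.

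**Step 4: four ordered grades.** Simulated trials with the 2.8.1 cuts, normal falls with SD 15 to 40 percentage points, means set to give the plan's rates at the 30% cut, and a tie-corrected Wilcoxon rank-sum test.

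| Power per comparison | vs heat | vs plaster |
|---|---|---|
| Yes/no rate, n = 33 | 28.4% | 44.0% |
| Four ordered grades, n = 33 | 37-40% | 56-59% |
| Full scale, n = 33, logistic | 39.5% | 58.1% |
| Full scale, n = 33, normal | 44.7% | 65.3% |
| Yes/no rate, n = 36 | 29.9% | 47.1% |
| Full scale, n = 36, normal | 48.0% | 69.2% |

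**Step 5: differences.**
- Yes/no to ordered grades: about 9 points (37 − 28) to 15 points (59 − 44).
- Yes/no to full scale: 11 points (39.5 − 28.4, logistic, n = 33) to 22 points (69.2 − 47.1, normal, n = 36).
- Ordered grades to full scale, normal model, n = 33: about 5 points (45 − 40) to 9 points (65 − 56).

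**Step 6: does this carry over to the points score?** Steps 3 and 4 model the percentage fall, whereas the analysis proposed below uses week-4 points adjusted for week 0. A simulation of that analysis on an integer score bounded at zero (assumed baseline 8 to 20 points, SD of percentage fall 20 to 40 points, 33 per arm) gave 40-42% against 28-29% for the rate (heat) and 60-63% against 42-45% (plaster). The gain is about 11 to 18 points, again conditional on the assumptions.

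**The case against.** The strongest reply is that 2.8.1 defines four ordered grades and nothing in the article fixes a yes/no primary test. The effective rate appears only in the sizing, and the test for a graded outcome may properly be left to a fuller document. That stands. A reader might infer a flat loss of 16 to 22 points from the primary outcome as written. The article does not support this: that range needs both the collapse to yes/no and the normal model. A reader might likewise infer that a 31% fall counts the same as a 90% fall. Under 2.8.1 these are two grades apart, and they become equal only after the collapse.

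Three further points have weight. The grades carry wording about symptoms, so they may not be a pure cut of the score. The full score is kept as a secondary outcome, so it is not lost to the trial. A response rate is also easier to read than an odds ratio or a difference in points. These are reasons to keep reporting the grades and the rate, but they do not justify basing the main test on the rate.

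Finally, recruitment began in April 2019 and the trial is registered, so replacing the primary endpoint is more than a change of wording and could look like outcome switching. That also stands and shapes the recommendation.

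**Conclusion.** The point holds conditionally. If the primary comparison is made on the collapsed effective rate, as 2.11 implies, it gives up about 9 to 15 points of power against the ordered grades and about 11 to 22 points against the full-scale score. If the grades are already meant to be tested as ordered, the remaining loss is only about 5 to 9 points on the normal model.

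The sizes rest on reading the effective rate as a fall of at least 30%, on the plan's own rates being true, and on an assumed distribution for the score. The full-scale analysis had the higher power than the yes/no rate in every model tried. It would be wrong to infer that a better scale rescues the design: at 33 to 36 per arm, the highest unadjusted figure here is 69%, and the sample size in 2.11 does not follow from its own rates on any scale considered.

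**What to change.** - **Section 2.12:** state that the four grades are compared as ordered categories, by a proportional-odds model or Wilcoxon rank-sum test, for herb-partitioned moxibustion against each control, and are not collapsed to effective versus invalid.
- **Sections 2.8.1 and 2.12:** add the week-4 syndrome score in points, adjusted for the week-0 score. Make it the primary test if an amendment made before unblinding is acceptable; otherwise name it as the key supporting analysis.
- **Reporting:** give the effective rate descriptively, and define it.
- **Section 2.11:** restate the power for the chosen scale, with its assumed distribution, and say that it remains below 80%.

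**Cost.** No new data, visits or participants. A common odds ratio or mean difference is less direct than a rate, which the descriptive report partly offsets. Specifying an ordered test leaves the endpoint as it is. Changing the primary endpoint itself after recruitment began needs a documented protocol amendment and a registry update.

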#### Inclusion criteria

2.4.2

Participants meeting all of the following criteria will be considered for inclusion:

(1)diagnosed as having simple obesity according to the diagnostic criteria;(2)aged between 18 and 45 years old;(3)Waistline: male≥ 95 cm, women≥85 cm;(4)Being able to fully understand and voluntarily sign informed consent.

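### The primary outcome divides by a TCM syndrome score that the entry criteria do not require to be above zero, so it can be incomputable for an eligible participant

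*Protocol article*

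**What the plan says.** **Outcome.** Section 2.8.1 calculates the primary outcome as "Integral variation formula (Nimodipine method: [(pre-treatment score-post-treatment score)/pre-treatment score] X100" per cent, and states: "This index will be assessed on week 4". The result is cut into four grades, each pairing a verbal description of symptoms with a score band:

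- The top grade needs "the syndrome score is reduced by ≥85" per cent.
- The lowest grade of response needs "syndrome scores decreased by <50%, but ≥30" per cent.
- Non-response is where "the syndrome score was reduced by <30" per cent.

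**Score.** Section 2.8.4 says: "The main clinical symptoms of simple obesity of spleen deficiency and dampness resistance type were divided into 4 levels", namely "no (0 point), mild (1 point), medium (2 points) and heavy (3 points". The points are summed to a total, measured at weeks 0 to 4. The number of symptoms is not given.

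**Entry.** Section 2.4.2 requires that a participant is "diagnosed as having simple obesity according to the diagnostic criteria", is aged 18 to 45, has a waistline of at least 95 cm (men) or 85 cm (women), and consents. The diagnostic criteria in 2.4.1 are BMI and waist circumference. None of the nine exclusions in 2.4.3 concerns the syndrome or a low score.

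**Analysis.** Section 2.12 commits to analysing all participants under both intent-to-treat and per-protocol principles. It compares groups by ANOVA, or a non-parametric equivalent, on change from baseline.

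**The concern.** The trial recruits people with simple obesity but judges success on the symptoms of one TCM type. Nothing in the entry criteria ensures that a participant has those symptoms. The Discussion names several TCM routes to obesity, of which spleen deficiency is only one, so the article itself allows for obese participants of another type.

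Two consequences follow. A participant with no scored symptoms at week 0 has no denominator, and the promise to analyse everyone cannot be kept for that person on the primary outcome. A participant with very few scored symptoms can meet a response band on the smallest change the scale can record. Participants know their treatment (section 2.6), so a one-step change in a symptom grade is thin evidence of an effect.

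Small numbers of such participants could matter. Section 2.11 plans on 33 per group, so one participant is worth 1/33 = 3.0 percentage points of an arm's response rate. The smaller planned difference is 0.80 - 0.65 = 0.15, or 0.15 x 33 = 4.95, about five participants.

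**Working it through.** The plan states no figure for this point that could be reproduced. The check applies its own formula to whole-number baselines.

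**Inputs**
- Formula and cut-points of 30%, 50% and 85%: section 2.8.1.
- Whole points per symptom, with 0 allowed: section 2.8.4.
- No syndrome or minimum-score condition: sections 2.4.1 to 2.4.3.
- Assumption: response means any grade except the lowest, i.e. a fall of at least 30%. The article does not say which grades make up its effective rate.

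**Step 1: baseline 0.** The formula is (0 - post)/0. If the week-4 score is also 0 this is 0/0; if the score has risen it is a negative number divided by zero. Neither has a value. The verbal descriptors do not help, since there are no scored symptoms to improve.

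**Step 2: value of a one-point fall.** Percentage fall = 1/baseline x 100.

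| Week-0 score | One-point fall | Numeric band met |
|---|---|---|
| 1 | 1/1 = 100% | top grade (at least 85%) |
| 2 | 1/2 = 50% | second grade (50% to under 85%) |
| 3 | 1/3 = 33.3% | third grade (30% to under 50%) |
| 4 | 1/4 = 25% | non-response (under 30%) |
| 5 | 1/5 = 20% | non-response |

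A single point takes a participant from no change to a response band only at baselines of 1 to 3.

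**Step 3: would a numerical floor cure this?** A minimum of 4 removes the zero denominator and the cases in the first three rows. It does not stop one point from deciding response at the 30% edge:
- Baseline 7: 2/7 = 28.6%, 3/7 = 42.9%.
- Baseline 10: 2/10 = 20%, 3/10 = 30%.
- Baseline 17: 5/17 = 29.4%, 6/17 = 35.3%.

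At baseline 4 itself, one point is 25% and two points are 50%, so the third grade cannot be reached at all. No figure in the article singles out 4.

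**Step 4: the analysis set.** Section 2.12 includes all participants. By step 1, a participant with a week-0 score of 0 cannot be graded. The two sections conflict for that participant, and the article gives no rule to resolve it.

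**The case against.** **Frequency.** The score sums several symptoms, so totals of 0 to 3 may be rare. Section 2.8.4 also describes the score as the standard for establishing the syndrome and takes it at week 0, which suggests that the syndrome is looked at on entry. The point on frequency stands: the article does not show that low scores are common. But the remark sits under outcomes and is not an entry condition, and 2.4.2 presents its list as the criteria that must all be met.

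**Verbal descriptors.** A reader might infer that a fall from 2 to 1 simply counts as the second grade. The document does not support that, because the grade also requires symptoms to be obviously improved. Only the numeric part is met. The case is strongest at 0, and at a fall from 1 to 0, where the symptom has gone.

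**Proportional endpoints.** A reader might infer that high scorers are treated unfairly: 30% needs 4 points from 12 (0.30 x 12 = 3.6) and 6 from 18 (0.30 x 18 = 5.4). That is inherent in a proportional endpoint and is not an error. Nor do the documents show that baseline imbalance biases the comparison. Randomisation balances the scores on average, and chance imbalance is covered by the type I error rate.

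**Handled elsewhere.** The syndrome score is also a secondary outcome, and section 2.12 appears to compare its change, which is defined at baseline 0. A computational rule for a zero denominator could sit in an analysis plan that is not shown. Both points soften the concern. Neither makes the printed entry criteria fit the printed primary outcome.

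**Conclusion.** The concern holds as a mismatch between sections 2.4.1 to 2.4.3 on one side and 2.8.1 with 2.8.4 on the other. An eligible participant can have an undefined primary outcome, contrary to the analysis of all participants in 2.12. At week-0 scores of 1 to 3, a one-point fall meets the numeric part of a response category.

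The arithmetic is certain, but the number of participants affected is unknown, since neither the item count nor the baseline distribution is given. It would be wrong to conclude that the primary result is invalid or that many responses will rest on a single point. The conclusion assumes that the inclusion list is complete as printed and that response means a fall of at least 30%. It is worth correcting because the correction is cheap.

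**What to change.** 1. Reconcile 2.4.2 with 2.8.1 and 2.8.4: for further enrolment, require the scored syndrome (spleen deficiency and dampness type) with a week-0 score above zero. Do not set a fixed 4-point floor, for the reasons in step 3 of the working.
2. Keep every participant already randomised, whatever the week-0 score.
3. In 2.12, pre-specify ANCOVA of the week-4 syndrome score on arm and week-0 score, in place of the unadjusted ANOVA on change. It is defined at a week-0 score of 0 and does not depend on the percentage bands, though it still needs a week-4 score. Make it supportive of the graded primary outcome. Requiring the two to agree would add a second hurdle with no rule for discordant results.

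**Cost.** No new data are needed, because the score is already taken at weeks 0 and 4. Some candidates may no longer qualify, which could slow recruitment, and the conclusion narrows from simple obesity to participants with the scored syndrome. Recruitment runs from April 2019, so participants enrolled before and after the change would have entered under different criteria, and the report should say so. Non-zero scores of 1 to 3 remain possible; the ANCOVA shows whether the result depends on them.
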